### Sample size evaluation

Assuming a true difference in means between the test and the reference group of 5 units, and a pooled standard deviation of 20 units, the study would require a sample size of 198 patients for each group (i.e. a total sample size of 396, assuming equal group sizes), to achieve a power of 80% and a level of significance of 5%, for declaring that the robotic TKA is superior to traditional TKA at 10 units margin of superiority, assuming a minimum clinically important difference for the WOMAC total subscale after TKA of 10 points [22].

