### Statistical analysis

All statistical analyses will be conducted by the main author (FM). For descriptive statistics, arithmetic mean and standard deviation shall be used. The unpaired t-test will be performed to assess baseline comparability, with values of *P* > 0.05 considered satisfactory. Data items will be collected by the assessors prospectively and entered into Microsoft Excel Spreadsheet Software version 2020 (Microsoft Corporation, Redmond, US). To compare robotic TKA versus freehand TKA, the IBM SPSS version 25 will be used. For continuous and binary data, the mean difference (MD) and odds ratio (OR) effect measures will be used. Standard error and 95% of confidence interval will be also evaluated. The null hypothesis will be that no difference between the two techniques exists. Both *χ*^2^ and unpaired *t*-test will be performed to evaluate whether the null hypothesis can be refused. Values of *P* < 0.05 were considered statistically significant. To evaluate the accuracy of implant positioning of robotic versus conventional TKA with regards to the pre-operative planning the standard deviation from the optimal implant alignment according to the patient anatomy will be evaluated using the IBM SPSS version 25.

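### The claimed 80% power for superiority by 10 points cannot hold at an assumed difference of 5, and the planned t-test, read as two-sided, has about 70%

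*Protocol article*

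**What the plan says.** The Sample size evaluation section gives all its design figures in one sentence:

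- Assumed effect: "Assuming a true difference in means between the test and the reference group of 5 units".
- Variability: "a pooled standard deviation of 20 units".
- Size: "the study would require a sample size of 198 patients for each group", that is, "a total sample size of 396, assuming equal group sizes".
- Power 80%, significance level 5%, with no statement of one- or two-sided.
- Claim to be supported: "for declaring that the robotic TKA is superior to traditional TKA at 10 units margin of superiority".
- Link to clinical relevance: "assuming a minimum clinically important difference for the WOMAC total subscale after TKA of 10 points".

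The Statistical analysis section sets a different hypothesis: "The null hypothesis will be that no difference between the two techniques exists". It is to be tested with an unpaired t-test for continuous data, with P < 0.05 as the threshold and 95% confidence intervals. That section mentions neither a margin nor a one-sided test.

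**The concern.** Declaring superiority at a 10-unit margin means rejecting the hypothesis that the benefit is 10 or less. A trial planned on a true benefit of 5 assumes that this hypothesis is true. The power statement therefore contradicts its own assumption, whichever way the scale is scored.

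The analysis section then tests for a difference from zero, so the stated 80% may not apply to that test either.

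The reading of the result is at stake. Under the analysis section, an observed difference of about 4 points is significant. Under the sample size section, about 13.3 points would be needed. The protocol's own minimum clinically important difference of 10 lies between the two. A result of 5 or 6 points could be called positive or negative depending on which section is followed, and a significant but small difference could be reported as meeting a design described as superiority by 10 units.

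**Working it through.** **Inputs.** True difference 5, SD 20, 198 per group, power 80%, level 5% and margin 10 come from Sample size evaluation. The null of no difference, the unpaired t-test, P < 0.05 and the 95% CI come from Statistical analysis.

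**1. Reproducing 198.** The formula is n per group = 2 × SD² × (z_α + z_β)² / d², where d is the distance between the assumed truth and the null value.

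- One-sided 5%, d = 5: 2 × 20² × (1.645 + 0.842)² / 5² = 197.8, so 198. This matches.
- Two-sided 5%, d = 5: 2 × 20² × (1.960 + 0.842)² / 5² = 251.2, so 252 (253 with the t distribution). This does not match.

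The stated figure therefore corresponds to a one-sided 5% level and a distance of 5. The protocol does not show where the 5 came from. It could be a true difference of 5 against a null of zero, or the gap between 5 and 10 with the sign lost. A non-inferiority formula with margin 10 and a true difference of 5 also gives 198. None of these is a superiority test at a margin of 10 with a true benefit of 5.

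**2. The stated claim.** SE = 20 × √(2/198) = 2.010.

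- To reject a benefit of 10 or less at one-sided 5%, the observed difference must exceed 10 + 1.645 × 2.010 = 13.3.
- Probability of this when the truth is 5: 1 − Φ(1.645 + 5/2.010) = 1 − Φ(4.13) = 0.000018, about 0.002%. The noncentral t gives the same to two figures.
- At one-sided 2.5% it is about 0.0004%.
- More patients lower it: at 400 per group, SE = 1.414 and the probability is about 1 in 10 million.
- True difference needed for 80% power with 198 per group: 10 + (1.645 + 0.842) × 2.010 = 15.0.

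**3. The planned test (zero difference, two-sided 5%).**

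- Power at 198 per group for a difference of 5: Φ(5/2.010 − 1.960) = 70.1%, or 69.9% with the noncentral t.
- Smallest observed difference that is significant: 1.960 × 2.010 = 3.9, about 4 points.
- Difference detectable with 80% power: (1.960 + 0.842) × 2.010 = 5.6 points.
- Size for 80% power at 5 points: 253 per group (t-based), 506 in total, which is 110 more than 396.

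**4. The same test one-sided at 5%.** Power for a difference of 5 is 80.0% (79.9% with the t distribution).

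**5. Effect of losses (assumption, not in the protocol).** If 10% are lost or excluded, about 178 per group remain. SE = 20 × √(2/178) = 2.120, and two-sided power is Φ(5/2.120 − 1.960), about 65%.

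**The case against.** The strongest reply is that the arithmetic is sound. The figures 198 and 396 reproduce exactly, and a one-sided 5% test of zero difference does have 80% power. The protocol never uses the word two-sided, so the 70% rests on an inference. This stands as a qualification. The inference is still the natural one: the null is no difference in either direction, the threshold is P < 0.05, and the intervals are 95%. The one-sided reading would also have to be stated, and it too abandons the 10-unit margin.

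The margin may also be the intended part and the 5 the slip. The protocol ties 10 points to clinical importance, and a true difference of 15 would give 198 per group one-sided. That cannot be excluded, but it would need a justified assumption of 15 and a test against 10, and the protocol contains neither.

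Two smaller points are fair. The 0.002% is strictly a false-positive probability, because the assumed truth satisfies the null; the essential fact is that no sample size gives 80%. And the analysis section names no endpoint for its null, so applying the test to the WOMAC total follows from the sample size section, where that score appears with the 10-point difference.

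None of this reconciles the two sections. They are positive statements that cannot all hold, so neither an unseen analysis plan nor the brevity of an article explains them.

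**Conclusion.** The concern holds. The stated 80% power fits neither the stated claim nor the planned test. For superiority by more than 10 points with a true difference of 5, the probability of success at 198 per group is about 0.002% and cannot be raised by recruiting more. For the t-test of no difference, power is 70%, so the type II error is 30% rather than the implied 20%. The fault is the pairing of margin, assumed difference and test; the division that produced 198 is correct.

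These figures rest on the protocol's SD of 20, 198 analysed per group, an unadjusted comparison and, for the 70%, a two-sided 5% level. As this is the only power statement in the protocol, it must be corrected.

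**What to change.** Remove the 10-unit superiority margin from Sample size evaluation. Name the hypothesis tested: difference in WOMAC total equal to zero, two-sided 5%, as the analysis section implies. Restate the figure: with SD 20 and no adjustment, 198 per group gives 70% power for 5 points, or 80% for 5.6 points. Keep the 10 points only as the yardstick for judging the 95% confidence interval.

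The cost is a rewritten paragraph and a less favourable stated power, with no extra patients. Adjusting for the baseline score would recover the power if its correlation with the outcome is about 0.5 (an assumption). The SD then becomes 20 × √(1 − 0.5²) = 17.3, SE = 1.741, and power is Φ(5/1.741 − 1.960), about 82%. With 178 per group it is about 78%.

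Two other repairs are coherent:

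- Keep 5 points and 80% power, and plan about 253 per group, 110 more patients in all. The protocol cites roughly 2000 knee replacements a year and ten years of recruitment.
- Keep the 10-point margin, justify an assumed difference well above 10 (15 gives 198 per group at one-sided 5%), and change the analysis to test against that margin.

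Whichever is chosen, the sample size and analysis sections must state the same margin, sidedness and test.

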### Statistical analysis

All statistical analyses will be conducted by the main author (FM). For descriptive statistics, arithmetic mean and standard deviation shall be used. The unpaired t-test will be performed to assess baseline comparability, with values of *P* > 0.05 considered satisfactory. Data items will be collected by the assessors prospectively and entered into Microsoft Excel Spreadsheet Software version 2020 (Microsoft Corporation, Redmond, US). To compare robotic TKA versus freehand TKA, the IBM SPSS version 25 will be used. For continuous and binary data, the mean difference (MD) and odds ratio (OR) effect measures will be used. Standard error and 95% of confidence interval will be also evaluated. The null hypothesis will be that no difference between the two techniques exists. Both *χ*^2^ and unpaired *t*-test will be performed to evaluate whether the null hypothesis can be refused. Values of *P* < 0.05 were considered statistically significant. To evaluate the accuracy of implant positioning of robotic versus conventional TKA with regards to the pre-operative planning the standard deviation from the optimal implant alignment according to the patient anatomy will be evaluated using the IBM SPSS version 25.

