### Data to be collected

On admission, the demographic information (age at surgery, BMI, sex), stage of OA according to the Kellgren-Lawrence classification [16], PROMs, and blood values of each patient will be collected on admission. Concerning the blood values, the haematocrit, haemoglobin, and C-reactive protein (CRP) will be collected preoperatively, on the first and fifth postoperative days. The blood tests will be conducted on admission, postoperative day (POD) 1 and 5 by dedicated healthcare personnel. To assess ROM, the neutral-zero method shall be used [17], using a standard baseline plastic 360-degree plastic pocket goniometer with flexion-hyper extension gauge (ProHealthcareProducts.com, Park City, US). ROM surgery will be assessed by moving the foot from a neutral starting position (neutral position in extension) in flexion and extension. ROM data will be collected on admission, on POD 1, 2, 3, 4, 5, and at each follow-up appointment by medical personnel who has not performed the index surgery. The German version of the Western Ontario and McMaster Universities Osteoarthritis Index (WOMAC) [18] and the visual analogue rating scale of health-related quality of life [19] will be used to rate the clinical outcomes. The patients will complete the questionnaires at admission and at each post-operative follow-up appointment. To evaluate the activity level of the patients included in the trial, the German version of the Tegner score will be administered [20]. In addition, a further seven questions Likert-like questionnaire shall be administered to all patients. This questionnaire is routinely used at our institution to rate the function of the knee in patients who undergo TKA. The questionnaire enquires about the activities related to the knee, post-operative overall patient satisfaction, patient satisfaction with the function of the knee, and information concerning walking distance. The Likert-like questionnaire is reported in Fig. 3, and the German version is available in Additional file 1.

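### Baseline balance is judged by t-tests with P > 0.05 as the pass mark, and outcomes are compared without using the baseline values collected; adjustment would add precision, by an amount the protocol does not let us fix

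*Protocol article*

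**What the plan says.** All places are in the Methods of the protocol article.

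- **Statistical analysis, baseline:** "The unpaired t-test will be performed to assess baseline comparability". A P-value above 0.05 is taken as satisfactory.
- **Statistical analysis, outcomes:** "For continuous and binary data, the mean difference (MD) and odds ratio (OR) effect measures will be used". The tests named are the chi-square and the unpaired t-test, against a null of no difference, at P < 0.05. No covariate is named.
- **Data to be collected:** for WOMAC and the quality-of-life scale, "The patients will complete the questionnaires at admission and at each post-operative follow-up appointment". ROM, haematocrit, haemoglobin and CRP are also measured at admission and again after surgery.
- **Sample size evaluation:** the calculation takes an SD of 20 and a difference of 5 between the arms, and arrives at 198 per group for 80% power at the 5% level. Its stated purpose is "for declaring that the robotic TKA is superior to traditional TKA at 10 units margin of superiority". Neither the sidedness of the test nor a baseline-to-follow-up correlation is given. The text does not say whether the SD belongs to the follow-up score or to the change.

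**The concern.** A significance test of baseline values answers the wrong question. If allocation is random, any difference is due to chance by construction, and the test will flag some variables in a sound trial. If allocation is not random, or patients drop out selectively afterwards, a P-value above 0.05 does not show that the arms are alike. The pass mark can therefore cast doubt on a good trial or reassure about a poor one.

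The outcome comparison then ignores the admission values. A chance baseline difference stays in the estimated treatment effect, and the outcome variance that baseline explains stays in the standard error. The cost is precision that the collected data could supply.

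**Working it through.** **Inputs from the protocol:** difference 5, SD 20, 198 per arm, power 80%, significance 5%, margin 10.

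**Assumed, not in the protocol:** baseline SD 20; correlation r between baseline and follow-up WOMAC of 0.3 to 0.6; losses or exclusions of 0 to 20%; independent baseline tests.

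**1. The stated sample size.** n per arm = 2 × [SD × (z_alpha + z_beta) / difference]².
- One-sided 5%: 2 × (20/5)² × (1.645 + 0.842)² = 197.8, so 198. This matches.
- Two-sided 5%: 2 × (20/5)² × (1.960 + 0.842)² = 251.2, so 252. This does not match.

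**2. Power at 198 per arm, unadjusted.** SE = 20 × √(2/198) = 2.01, and 5/2.01 = 2.487.
- One-sided: Φ(2.487 − 1.645) = 80.0%.
- Two-sided: Φ(2.487 − 1.960) = 70.1% (69.9% by the exact t calculation).

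**3. What the pass mark lets through.** The largest non-significant baseline gap is 1.96 × 2.01 = 3.94 points (3.95 with the t quantile). At an assumed slope of 0.5 this moves the unadjusted contrast by 0.5 × 3.94, about 2 points. That is the extreme at the threshold, not a typical imbalance.

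**4. What the pass mark flags by chance.** The continuous admission variables are age, BMI, haematocrit, haemoglobin, CRP, ROM, WOMAC and the quality-of-life scale, so eight. The chance of at least one P < 0.05 under perfect randomisation is 1 − 0.95⁸ = 34%. Adding the Tegner score gives 1 − 0.95⁹ = 37%, and twelve variables give 46%. Several of these variables are correlated, so the figures are indicative only.

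**5. Gain from adjustment.** Taking SD 20 as the follow-up SD, the residual SD is 20 × √(1 − r²). Two-sided 5%, difference 5:

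| r (assumed) | Residual SD | Power at 198 per arm | n per arm for 80% |
|---|---|---|---|
| 0 | 20.00 | 70.1% | 252 |
| 0.3 | 19.08 | 74.1% | 229 |
| 0.4 | 18.33 | 77.5% | 211 |
| 0.46 | 17.76 | 80.0% | 199 |
| 0.5 | 17.32 | 81.9% | 189 |
| 0.6 | 16.00 | 87.5% | 161 |

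Break-even: r = √(1 − 198/251.2) = 0.46. With 10% lost or excluded (178.2 per arm) it is √(1 − 178.2/251.2) = 0.54. With 20% (158.4 per arm) it is 0.61.

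**6. The margin.** If superiority must be shown beyond 10 units while the true difference is 5, one-sided power is Φ((5 − 10)/2.01 − 1.645) = Φ(−4.13), below 0.01%. A smaller residual SD makes it lower still.

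**The case against.** **The article is a condensed protocol, and an analysis plan may adjust for baseline.** This does not remove the point. The article leaves neither step open: it names the baseline test, its pass mark and the outcome tests. A plan that adjusted for baseline would depart from the published text.

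**No action follows from a failed baseline test, and under true randomisation the unadjusted t-test is valid.** Both statements stand. The confidence interval already allows for chance imbalance. A reader might infer that the planned comparison is biased or invalid; under random allocation it is not, and adjustment is a gain in efficiency. If allocation or later exclusions are selective, adjusting for a baseline score does not cure that either.

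**The power argument rests on readings that the protocol does not confirm.** This also stands. A reader might infer that adjustment recovers all the missing power at no cost and makes 198 per arm sufficient. The documents do not support that, for four reasons:
- The shortfall from 80% to 70.1% exists only if the test is two-sided. The null of no difference makes that plausible, but the sample size section does not say so.
- No correlation is given, and at 0.3 or 0.4 adjustment falls short of 80%. The surgical section excludes patients who deviate from the planned procedure or rehabilitation, which raises the correlation needed.
- SD 20 may not be the follow-up SD. If it is already net of baseline, nothing more is gained. If it is the SD of change, the variance factor (with equal variances at both times) is (1 + r)/2 instead of 1 − r², and the table changes except at r = 0.5.
- Adjustment cannot help where the assumed 5-unit effect lies inside a 10-unit margin.

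**Adding surgeon to the model could do harm.** This is correct. The Randomisation and blinding section sends patients either to surgeons who operate with the robot or to others who operate freehand. Surgeon then appears nested within arm, and a fixed surgeon term would be aliased with treatment.

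**Conclusion.** The point holds as one about a stated method. P > 0.05 is not a valid criterion of baseline comparability. At 198 per arm and an assumed baseline SD of 20 it passes a WOMAC gap close to four-fifths of the assumed effect (3.94/5 = 0.79). The planned outcome comparison also leaves unused the admission values that the trial collects.

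The precision gain from using them is real for any non-trivial correlation, but its size is unknown. Under the three conditions in the working (two-sided 5%, SD 20 as the follow-up SD, any difference as the target), power rises from 70.1% to between 74.1% and 87.5% over the assumed correlations. The criticism of the balance rule depends on none of these conditions. Sidedness and the 5-unit versus 10-unit conflict are separate questions that this change leaves open.

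**What to change.** In the Statistical analysis section:

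1. Delete the baseline t-tests and the P > 0.05 rule. Present baseline values by arm descriptively.
2. For each continuous outcome with a baseline measurement, prespecify a linear model of the follow-up value on arm plus its own baseline value. Report the adjusted mean difference with its 95% CI. Keep the unadjusted t-test as supportive.
3. Include no fixed surgeon term while surgeon appears nested within arm.
4. If adjustment is cited in support of the sample size, state the assumed correlation and its source, say which SD the 20 units refer to, and allow for losses and exclusions. Resolve the sidedness of the test and the 5-unit versus 10-unit conflict separately.

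Items 1 to 3 cost wording only: no new data, visits or patients, and the SPSS version already named fits such models. The text should be fixed before outcome data are analysed, so that covariates are not chosen in response to baseline P-values.

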## Methods

### Study protocol

The present study shall be conducted in accordance with the SPIRIT 2013 statement (defining standard protocol items for clinical trials) [15]. All patients who will receive a TKA at the Department of Orthopaedic Surgery of the Eifelklinik St. Brigida in Simmerath (Germany) will be prospectively invited to participate in the present investigation. The recruitment will start on January 1, 2023, and will stop on January 1, 2033. The present study shall be conducted according to the principles of the Declaration of Helsinki. The shall authors receive no financial support for the research, authorship, and/or publication of this article. The protocol of the study has been prospectively registered and approved by the German Registry of Clinical Trials (ID DRKS00030614). Ethics approval has been received from the North Rhine Medical Council, Dusseldorf, Germany (ID 2022374).

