### Randomisation and blinding

The present study is a protocol for a single-blind randomised controlled trial in which each group of participants is exposed to only one of the study interventions. Patients will be randomly allocated to robotic-assisted TKA or to conventional freehand TKA. All patients in whom a TKA is indicated will be sequentially allocated in a 1:1 ratio to surgeons who perform robotic-assisted TKA or to those who perform conventional freehand TKA at the time of their outpatient appointment. All patients, irrespective of their allocation, will follow the same clinical, imaging, and anaesthesiologic pre- and post-surgical pathways. Patients will be blinded to the allocation until the first postoperative days. Surgeons and personnel involved in the clinical management of the patients will be unblinded to the allocation. Data curacy and collection will be conducted by two assessors blinded to group allocation and not involved in the clinical management of the patients. Assessors will retrieve patient data at the following follow-up times: admission, perioperatively (from access to discharge), at 6 weeks, 12 months, and every 24 months postoperatively. Data from patients will be collected once the learning curve has been reached.

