**Fig. 3 Fig3:**
[figure not shown]
Likert-like questionnaire

Concerning complications, the number of wound healing complications, haematomas, anterior knee pain, periprosthetic fractures, deep infections, aseptic loosening, deep vein thromboses, and surgical revision will be collected at discharge and each follow-up.

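### Revision, loosening, fracture and deep infection build up over staggered, open-ended follow-up, but the plan names only an odds ratio and chi-square for them, with no time horizon

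*Protocol article*

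**What the plan says.** All references are to the protocol article.

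- **Method.** Statistical analysis: "For continuous and binary data, the mean difference (MD) and odds ratio (OR) effect measures will be used". A chi-square and an unpaired t-"test will be performed to evaluate whether the null hypothesis can be refused". No method that uses time at risk is named.
- **Events.** Data to be collected (text below Fig. 3): besides early complications, "periprosthetic fractures, deep infections, aseptic loosening, deep vein thromboses, and surgical revision will be collected at discharge and each follow-up".
- **Visits.** Randomisation and blinding: after the perioperative period, data are retrieved "at 6 weeks, 12 months, and every 24 months postoperatively". No last visit is given.
- **Entry.** Study protocol: "The recruitment will start on January 1, 2023, and will stop on January 1, 2033".
- **Allocation.** Randomisation and blinding: patients are "sequentially allocated in a 1:1 ratio to surgeons who perform robotic-assisted TKA or to those who perform conventional freehand TKA".
- **Learning curve.** The same section, repeated in the Discussion: "Data from patients will be collected once the learning curve has been reached". The sentence names no arm.

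**The concern.** Some of the listed complications are settled early. Revision, aseptic loosening, periprosthetic fracture and deep infection are not: their number grows for as long as patients are watched. With staggered entry and open-ended visits, time at risk can differ between patients by years. An odds ratio from a two-by-two table has no place for time at risk, so it can be applied in only two ways:

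- **Pooled over all follow-up.** A patient observed briefly and one observed for years count alike. The risk in each arm then belongs to no stated time after surgery and depends on when the data are cut.
- **Separately at each visit.** The time point is defined, but patients who have not yet reached that visit drop out of the comparison, and their event-free time is lost.

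Neither gives an estimate of implant survival, which the Introduction lists among the hoped-for benefits of robotic surgery. If follow-up also differed between the arms, the pooled odds ratio would be biased as well as hard to interpret.

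**Working it through.** The article gives no figure for complications, so there is none of its own to reproduce here. The 198 patients per group in Sample size evaluation relate to WOMAC and are used below only as the arm size. They reproduce at one-sided 5%: 2 × (1.645 + 0.842)² × 20² / 5² ≈ 198.

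**Assumptions (not in the documents).** Constant hazard h of 0.5% to 2% a year; entry uniform from the start of the arm to year 10; one data cut at year C.

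**Formula.** If follow-up is uniform between a and b years, the pooled risk is p = 1 − [exp(−ha) − exp(−hb)] / [h(b − a)]. The odds ratio is [p₁/(1 − p₁)] / [p₀/(1 − p₀)].

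**1. Dependence on the analysis date.** With h = 1% and entry over years 0 to 10, a cut at year 10 gives follow-up of 0 to 10 years:

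p = 1 − (1 − exp(−0.10))/0.10 = 4.84%.

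Cuts at years 12, 15 and 20 give 6.72%, 9.48% and 13.89%. The hazard is the same throughout; only the date of analysis has changed.

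**2. Loss from per-visit odds ratios.** With the same entry and a cut at year 10, the share of patients with at least 5 years of follow-up is (10 − 5)/10 = 50%. The other half would add nothing to a five-year comparison, although they carry 2.5 years of observation on average.

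**3. Relative estimate when both arms enter together.** With no true effect the odds ratio is 1.00 at any cut. With a true effect and a cut at year 10:

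| True hazard ratio | Pooled odds ratio, h = 0.5–2% | Odds ratio at a fixed 10 years |
|---|---|---|
| 0.5 | 0.492–0.498 | 0.475–0.494 |
| 0.7 | 0.693–0.698 | 0.679–0.695 |

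Mixing exposure hardly moves the relative estimate.

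**4. If the robotic arm started later (hypothetical), no true effect.** For a 1-year lag, h = 1% and a cut at year 10, robotic follow-up is 0 to 9 years:

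p₁ = 1 − (1 − exp(−0.09))/0.09 = 4.37%; odds ratio = (0.0437/0.9563)/(0.0484/0.9516) ≈ 0.90.

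Over h = 0.5–2%, lags of 0.5, 1 and 2 years give about 0.95, 0.90 and 0.80. With a cut at year 15, a 2-year lag gives 0.89–0.90.

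At h = 1% and 198 per arm, the chi-square rejection rate rises from 5.0% with no lag to 5.6%, 7.4% and 10.9% for lags of 1, 2 and 3 years.

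**5. How wide the entry period might be.** The Discussion gives about 2000 knee replacements a year. If recruitment ended at 396 patients, it would take 396/2000 ≈ 0.2 years with everyone enrolled and 396/200 ≈ 2.0 years at 10% enrolment. Filling ten years would need 396/20,000 ≈ 2% enrolment. However, the article gives a stop date and does not say that recruitment closes at 396.

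**The case against.** The strongest reply is that little is shown to be wrong. The statistical section of a condensed article names general effect measures. It does not say that all follow-up is collapsed into one table, and horizons, data cuts and censoring are commonly set out elsewhere. Complications are only one group of many outcomes, and the sample size rests on WOMAC. This lowers the weight of the point. It does not remove it, because the article does not merely leave the method open: it assigns one that takes no account of time at risk, and a better one is readily available.

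Four stronger readings are tempting, and the documents support none of them:

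- **The odds ratio will favour robotic surgery because that arm starts later.** Allocation is concurrent and 1:1, and the learning-curve sentence speaks of patients without naming an arm. Because the curve is defined by robotic cases, it could be read as excluding early robotic patients only. The text does not say so, and it does not rule it out. A long lag also looks unlikely: with all 2000 patients a year allocated 1:1, one year would mean about 1000 robotic operations before the plateau.
- **Even a one-year lag would mislead badly.** With 198 per arm and h = 1%, expected events are 198 × 0.0484 ≈ 9.6 and 198 × 0.0437 ≈ 8.7. The approximate 95% interval around 0.90 is 0.35 to 2.3, so random error would far exceed the bias.
- **Follow-up will range from 0 to 10 years.** Ten years is the recruitment window. That range needs entry across the whole window and a single cut at its end, and no cut date is stated.
- **Deaths and losses will count as event-free.** No rule for either is given. This would follow from a pooled ever/never table, but the article does not say that one will be used.

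**Conclusion.** The point holds in a limited form. For events that accumulate over years, the named odds ratio and chi-square either give risks without a defined time (pooled) or discard partial follow-up (per visit). The cost is mainly in interpretation and information. Under the assumptions above, the pooled risk roughly doubles between a cut at year 10 and one at year 15 (4.84% to 9.48%), while the relative estimate under concurrent entry stays within about 0.02 of its fixed ten-year value. If entry is completed quickly, the spread in exposure is smaller still.

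No bias between the arms is shown. It would arise only if follow-up differed by arm, and the figure of about 0.90 for a one-year lag illustrates that case; it does not predict it. Hazards, lags and enrolment shares are all assumed. Severity is minor: a cheap improvement.

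**What to change.** - For surgical revision, aseptic loosening, periprosthetic fracture and deep infection, record the date of each event and of last contact. Analyse time from surgery to first event with Kaplan-Meier curves, a log-rank test and a Cox hazard ratio, censored at last contact. SPSS 25, the package already named, offers these.
- Keep odds ratios and chi-square for complications at fixed times that all patients are due to reach: discharge, 6 weeks and 12 months.
- State that data collection starts on one common date for both arms once the learning-curve condition is met, so that the condition cannot shorten follow-up in one arm only.

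The cost is a change of wording, two extra date fields and slightly more analysis. One limit remains: loosening found at a visit carries the date of detection, which is coarse when visits are 24 months apart.
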